**Methods:**

The study is a single-center randomized controlled trial (RCT) with two study arms - intensive diabetes mellitus care versus routine clinical care. Patients in the intensive arm will receive care from a multidisciplinary team consisting of an endocrinologist, diabetes nurse educator, dietitian, renal pharmacist and medical social worker for counselling. In addition, patients will be provided with tools for self-care empowerment such as glucometers, blood pressure monitors and android tablets to facilitate care, monitoring and education. Patients in the routine clinical care arm will receive standard clinical care. Follow up (FU) will be for 3 years. Primary outcomes include cardiovascular events, rate of progression of nephropathy and development of end-stage renal disease. Secondary endpoints include the proportions of patients with documented improved control of cardiovascular risk factors (HbA1c, blood pressure, low density lipoprotein-C (LDL-C), reduction in body weight), frequency of hypoglycemia, hospitalization days and changes in femoral IMT. We will also examine the prevalence of peripheral atherosclerosis and the predictive value and usability of lower extremity arterial ultrasound to predict cardio-cerebrovascular events, amputation and peripheral intervention.

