### Eligibility criteria

Patients will be considered eligible for the study if they fulfil the following criteria:
Aged 21–70 yearsPoorly controlled T2DM as defined by HbA1c ≥ 9%Nephropathy as defined by estimated GFR (eGFR) 30–60 ml/min and/or proteinuria classified as urine protein > 0.5 g/day and/or urine albumin:creatinine ratio (ACR) >30 mg/mmol on two consecutive measurements 3 months apart

Patients will be excluded from study participation if any of the following criteria are present:
Type 1 diabetes mellitus defined as a history of ketosis at diagnosis (acute symptoms with heavy ketonuria (urine value > 3+) or ketoacidosis) or continuous requirement of insulin within 1 year of diagnosis.Psychiatric conditions being treated by medications that adversely affect patients’ weight and stability of their mental health.Patients on weight loss medications or have had bariatric surgery, which may affect their mental health and compliance with dietary advice.Life expectancy < 12 months due to advanced cancer or other life-threatening conditions, such that they will not be able to perform self-care or complete 3 years of follow-up.Pregnant or lactating patients.

Patients will be withdrawn from the study if any of the following criteria apply:
The patient withdraws consentThe patient is no longer able to participate or the investigator, in discussion with the patient’s attending physician(s), decides to terminate participation on medical groundsThe patient becomes pregnant during the study

There will be no participant replacement in the study if a participant withdraws.

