### Allocation

Computer generated codes numbered 1–50 will be used to assign patients to either the intensive arm or the standard care arm. The randomization procedures are as follows:
The physician or nurse will explain to eligible patients about the international recommendation on performing regular follow-up to detect silent risk factors and complicationsThey will also explain to patients the need to assess the effectiveness of using a team to implement structured care by comparing the latter with usual careAfter the patient has signed the consent form, a study team member will open the envelope containing the randomization group and sign and date the envelopeThe signed envelope will be kept by the nurse in a secure place for audit purposesThe nurse will explain to the patient whether they have been randomized to the intensive arm or standard care arm and the assessment will proceed accordinglyThe nurse will keep a log of randomized patients and record status including study completion, premature discontinuation, withdrawal of consent or loss to follow-up

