#### Primary endpoints

The primary outcome measures are (1) rate of deterioration of chronic kidney disease (rate of decline of eGFR or worsening of proteinuria) or development of end-stage renal disease, whichever events happen and (2) cardiovascular events (composite events of acute myocardial infarction, revascularization procedures, heart failure, unstable angina, arrhythmia, stroke, transient ischemic attacks requiring hospital admissions) and related death, whichever events happen.

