### Statistical methods

Categorical data will be presented as frequency (percentage). Numerical data will be presented as mean (standard deviation (SD)), unless specified otherwise. Differences in baseline characteristics between two groups will be examined using the chi-square test or Fisher’s exact test for categorical variables and the two-sample *t* test or Mann-Whitney U test for continuous variables.

Logistic regression of binary outcomes such as cardiovascular events will be performed to determine the association between treatment group and potential risk factors and the outcomes. Relative risk (RR) (with 95% CI) will be calculatec. For continuous outcomes such as change in the MARS-5 and DDS17, linear regression will be used. Measure of tolerance for multicollinearity will be assessed. Coefficient B (with 95% CI) will be reported. The number of occurrences of hypoglycemia will be analyzed by Poisson regression. Measure of deviance will be checked and relative risk (RR) (with 95% CI) will be calculated.

*P* values < 0.05 will be deemed statistically significant. Statistical analysis will be performed using SPSS statistical software, version 19.0 (IBM Corp. Armonk, NY, USA). This RCT will be analyzed by the principle of intention to treat (ITT) and the per protocol (PP) approach.

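### The 3-year cardiovascular primary outcome is assigned to logistic regression, which ignores event timing and time at risk although withdrawal and loss to follow-up are foreseen

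*Protocol article*

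**What the plan says.** - **Model.** Statistical methods: "Logistic regression of binary outcomes such as cardiovascular events will be performed", relating treatment group and potential risk factors to the outcome. The effect measure follows: "Relative risk (RR) (with 95% CI) will be calculatec". No time-to-event or person-time method is named for this outcome.
- **Endpoint.** Primary endpoints: the second primary outcome is a composite of cardiovascular events ending "transient ischemic attacks requiring hospital admissions) and related death, whichever events happen". Deaths from other causes are outside it.
- **Horizon.** Abstract, Methods: "Follow up (FU) will be for 3 years".
- **Incomplete follow-up.** Eligibility criteria: "Patients will be withdrawn from the study if any of the following criteria apply", followed by withdrawn consent, inability to continue or medical grounds, and pregnancy. The same section adds: "There will be no participant replacement in the study if a participant withdraws". Under Allocation, the nurse's log is to "record status including study completion, premature discontinuation, withdrawal of consent or loss to follow-up". Harms also provides for withdrawing a patient whose wellbeing is judged to be at unacceptable risk.
- **Analysis sets.** Statistical methods names intention to treat and per protocol. The article does not say how a patient who leaves early without an event enters the logistic model.

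**The concern.** The Abstract sets out to study how fast complications progress, but the model chosen for a primary event outcome sees only whether an event was recorded. A patient observed for 6 months and one observed for 36 months carry the same weight if neither has an event, and an event in month 2 counts the same as one in month 35.

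A logistic model needs a yes or a no for every patient it includes. A patient who leaves early without an event has neither, so a coding rule must supply it. Each of the two simple rules distorts the absolute 3-year risk. Each also distorts the comparison if drop-out differs between arms.

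Unequal drop-out is plausible here but not established. The intensive arm has reminders between visits, tracking of missed appointments and six social-worker sessions. The standard arm has 4-monthly visits and nurse calls that the patient starts. Heavier contact could improve retention or add burden, so the direction is unknown.

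**Working it through.** The plan has no figure to reproduce. Its sample size rests on mean eGFR, and it gives no cardiovascular event rate and no drop-out rate. The rates below are assumptions chosen to show the range.

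**Inputs**
- From the protocol: 3 years of follow-up; 25 patients per arm.
- Assumed: true 3-year risk p = 30% in both arms; 3-year drop-out c = 10%, 20% or 30%; constant hazards; drop-out unrelated to event risk.

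**Formulas**
- Event hazard λ = −ln(1 − p)/3 = −ln(0.70)/3 = 0.1189 per year.
- Drop-out hazard μ = −ln(1 − c)/3.
- Observed and event-free at 3 years: S = (1 − p)(1 − c).
- Event observed before drop-out: E = λ/(λ + μ) × (1 − S).
- Drop-outs coded event-free: risk = E.
- Event-free drop-outs excluded: risk = E/(E + S).

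**Risks by coding rule (true value 30%)**

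| Drop-out | μ | S | Coded event-free | Excluded |
|---|---|---|---|---|
| 10% | 0.0351 | 0.63 | 28.6% | 31.2% |
| 20% | 0.0744 | 0.56 | 27.1% | 32.6% |
| 30% | 0.1189 | 0.49 | 25.5% | 34.2% |

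Worked case at 30% drop-out: λ = μ, so E = 0.5 × (1 − 0.49) = 0.255. Excluding event-free drop-outs gives 0.255/(0.255 + 0.49) = 0.342.

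**Relative risk, intensive over standard, true RR 1.00** (ratios from unrounded risks)
- Equal drop-out: 1.00 under either rule.
- Standard 10%, intensive 30%: 25.5/28.6 = 0.89 coded event-free; 34.2/31.2 = 1.10 excluded.
- Standard 30%, intensive 10%: 1.12 coded event-free; 0.91 excluded.

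**Relative risk when the true risks are 30% and 20% (true RR 0.667)**
- Equal 20% drop-out: 0.665 coded event-free; 0.674 excluded.
- 10% versus 30% drop-out, in either direction: 0.59 to 0.75 coded event-free; 0.61 to 0.74 excluded.

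**Set against this trial's precision** (drop-outs coded event-free, 10% versus 30%)
- Difference in expected events: 25 × (0.2856 − 0.2550) = 0.77 of one event.
- SE of log RR = √[(1 − 0.2856)/(25 × 0.2856) + (1 − 0.2550)/(25 × 0.2550)] = 0.47.
- Shift = ln(0.893)/0.466 = −0.24 SE. The two-sided type I error rises from 5% to about 5.7%.
- The 95% CI extends by a factor of about exp(1.96 × 0.466) = 2.5 in each direction.

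**The case against.** **A binary analysis is legitimate here.** All patients share a planned 3-year horizon, and a 3-year risk with an RR is a recognised summary in a 50-patient pilot. This stands in part. With complete or equal, non-informative follow-up the RR is nearly unaffected, and even the unequal case assumed above moves it by about a quarter of a standard error.

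**The coding rule may be in a document not shown.** This also stands. A reader might infer that patients who withdraw or are lost will count as event-free, so that event risk is underestimated. The article does not say so. They could equally be excluded, which raises the risk, or have their status imputed or traced through hospital records. The absence of the rule from the article is not the finding. The finding is the stated model, which needs such a rule and has no place for observation time.

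**Death from another cause as a non-event is not a bias.** A reader might take the restriction to related death ("and related death, whichever events happen") as biasing the risk. For a 3-year cumulative incidence it does not, because a patient who has died can no longer have a cardiovascular event. It is a choice of estimand that should be stated.

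**Differential drop-out is not shown.** Correct. The documents give no rates, and the design features point both ways.

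**Time-to-event methods are no cure-all.** Also correct. Censoring at last contact assumes that those who leave have the same future risk as those who stay, which is doubtful for withdrawal on medical grounds.

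What survives is that neither simple coding rescues the binary model when drop-out differs by arm, and that a method using the observed time is available at little cost.

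**Conclusion.** The point holds as a weakness in a stated analysis choice for a primary outcome, and it should be changed. Logistic regression discards event timing and time at risk over 3 years, in a protocol that itself expects incomplete follow-up.

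Under the assumed 30% risk and 10% to 30% drop-out, the absolute risk is off by about 1 to 5 percentage points, downwards if drop-outs are coded event-free and upwards if they are excluded. The RR is almost unchanged with equal drop-out. With 10% versus 30% drop-out it shifts by about 10% to 12%, in a direction that depends on the coding rule and on which arm loses more patients. That shift is small beside the imprecision of 25 patients per arm.

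These sizes rest on assumed rates, constant hazards and drop-out unrelated to event risk. The documents do not support the stronger claim that the planned comparison is biased in a known direction.

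**What to change.** For the cardiovascular primary outcome:

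1. Make the main analysis time from randomisation to first cardiovascular event or related death, censored at last contact, with unrelated death as a competing event.
2. Report 3-year cumulative incidence by arm with the Aalen-Johansen estimator, with a risk difference or ratio and 95% CI. Kaplan-Meier with unrelated deaths censored would overstate the risk and conflict with treating those deaths as competing.
3. Add a cause-specific Cox model, Firth-penalised if events are few, and report all-cause death alongside.
4. Record event and last-contact dates for every patient. The Allocation section mentions a status log, but the only date it specifies is the one on the randomisation envelope.
5. Keep the logistic analysis as supportive, with a stated rule for patients who have incomplete follow-up and no event.

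The cost is mainly analysis wording plus capture of dates. Hospital admissions and serious adverse events are already to be collected, so dating events should be feasible. A hazard ratio is added to the RR or replaces it. Censoring must be assumed non-informative, which does not repair health-related withdrawal. Ascertaining event status after withdrawal, where consent allows, would reduce that problem.

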### Randomization

There will be a total of 50 patients recruited, with 25 patients randomized to the intensive arm and 25 patients to the standard care arm. Randomization will be performed by a statistician using computer-generated random number sequence with an allocation ratio of 1:1 for each group.

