### Sample size

The proposed sample size of 25 participants in each group is adequate to estimate the mean of the eGFR between the two groups of participants, effect size (2.5-unit difference) using the *t* test (two-tailed alpha = 0.05 with statistical power of 0.80).

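### Logistic regression is the only stated between-arm method for binary outcomes with 25 patients per arm, and it gives no finite estimate if one arm has no events

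*Protocol article*

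**What the plan says.** The Randomization section plans a trial "with 25 patients randomized to the intensive arm and 25 patients to the standard care arm". In Statistical methods, the between-arm analysis of binary outcomes is stated once: "Logistic regression of binary outcomes such as cardiovascular events will be performed to determine the association between treatment group" and potential risk factors on one side and the outcomes on the other. A relative risk with 95% CI is to be calculated as well; how it is derived is not stated. The small-table tests appear in another role: "Differences in baseline characteristics between two groups will be examined using the chi-square test or Fisher’s exact test for categorical variables". The decision rule is that P "values < 0.05 will be deemed statistically significant". The section does not say whether the P value for treatment comes from a Wald, likelihood-ratio or score test.

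The example given for this model, cardiovascular events, is the second primary outcome. The first covers decline of eGFR or worsening proteinuria "or development of end-stage renal disease, whichever events happen". No event rate is given for any binary outcome in either arm.

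**The concern.** Logistic regression fitted by maximum likelihood fails when one arm has no events, even with treatment as the only term. The fitted odds ratio runs off to zero or infinity and its standard error grows without limit. The relative risk does not rescue the analysis: its point estimate is 0 (or undefined), and the usual log-scale interval does not exist.

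Two things are at stake. The trial could end with no usable effect estimate or interval for a binary outcome. And whether that outcome is called significant could depend on which test statistic the analyst reads from the model, a choice the protocol leaves open.

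**Working it through.** **Inputs.** From the protocol: 25 per arm, two-sided 0.05. Event risks are assumptions, because none is stated.

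**The plan's own figure.** The only sample-size figure concerns mean eGFR: 25 per group, a 2.5-unit difference, "two-tailed alpha = 0.05 with statistical power of 0.80". It cannot be reproduced because no SD is given; it would need an SD of 2.5 / [(1.960 + 0.842) × √(2/25)] = 3.15. It has no bearing on the binary outcomes, for which no power figure is stated.

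**Step 1: one table, 0/25 v 6/25.**
- *Model fit.* The event-free arm contributes 25 × ln(1 − p) to the log-likelihood. This keeps rising as p goes to 0, so there is no finite maximum. After 20 Newton iterations the coefficient is −20.1 with SE 8,039, giving Wald P = 0.998. The Wald P stays near 0.998 for every control count from 1 to 12.
- *Likelihood ratio, same model.* The log-likelihoods are 0 for 0/25, 6 ln 0.24 + 19 ln 0.76 = −13.777 for 6/25, and 6 ln 0.12 + 44 ln 0.88 = −18.346 for the pooled 6/50. G² = 2 × (18.346 − 13.777) = 9.14, P = 0.0025.
- *Fisher.* 2 × C(25,6)/C(50,6) = 2 × 177,100/15,890,700 = 0.022. Mid-P is 0.011 if both equally probable extreme tables get half weight, and 0.017 if only the observed table does. The figures below use the first definition.
- *Relative risk.* 0/0.24 = 0. The log-scale SE contains 1/0, so the interval is undefined.

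**Step 2: other control counts against 0/25.**

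| Control events | Wald P | Likelihood-ratio P | Fisher P |
|---|---|---|---|
| 3 | 0.998 | 0.037 | 0.235 |
| 4 | 0.998 | 0.015 | 0.110 |
| 5 | 0.998 | 0.006 | 0.0502 |
| 6 | 0.998 | 0.0025 | 0.022 |
| 8 | 0.998 | 0.0004 | 0.004 |
| 10 | 0.998 | 0.00005 | 0.0006 |

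**Step 3: how often is an arm empty?** (1 − p)^25 is 0.28 at 5% risk, 0.07 at 10%, 0.017 at 15% and 0.004 at 20%.

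**Step 4: type I error and power, summing binomial probabilities over all 26 × 26 tables** (an empty cell counts as non-significant for Wald).

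With a common risk, the likelihood-ratio test rejects in 7.1% of trials at 5% risk and 8.1% at 10%. Mid-P stays at or below 4.5% for the common risks of 5% to 30% that were checked.

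| Assumed risk, control v intensive | Wald | Fisher | Mid-P | Likelihood ratio | Empty intensive arm and Fisher P < 0.05 |
|---|---|---|---|---|---|
| 30% v 2% | 24% | 72% | 79% | 89% | 49% |
| 30% v 5% | 37% | 55% | 63% | 71% | 22% |
| 20% v 2% | 8% | 30% | 43% | 67% | 23% |
| 30% v 10% | 32% | 30% | 39% | 45% | 6% |
| 40% v 20% | 32.5% | 23% | 32.4% | 35% | 0.4% |
| 30% v 15% | 20% | 15% | 21.5% | 26% | 1.4% |
| 20% v 10% | 7.8% | 8.6% | 12.0% | 18% | 3% |

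The likelihood-ratio power is inflated by that test's excess type I error where risks are low.

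**Step 5: does an interval exist at 0/25 v 6/25?** The Miettinen-Nurminen upper limit for the relative risk R solves (0 − 0.24R)/√{(50/49)[p₁(1 − p₁) + R²p₂(1 − p₂)]/25} = −1.96, where p₁ = R·p₂ are the restricted estimates. At R = 0.593, p₂ = 0.155 and p₁ = 0.092; the numerator is −0.142, the denominator 0.0727 and the ratio −1.96. The 95% CI is 0 to 0.59.

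**The case against.** The strongest objection is that the protocol never names the Wald test. A reader might infer from Step 1 that a striking programme effect would be reported as non-significant. The document does not support that without a condition: it follows only if the Wald P is the one used, and the likelihood-ratio test of the same model gives P = 0.0025 at 0 v 6. This stands. It does not clear the plan, because that test brings no finite estimate and is anti-conservative at low risks.

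Second, the harmful case is narrow. The arm must be empty, and Fisher's test also misses 0 v 1 to 0 v 5. The cardiovascular endpoint is a broad composite over 3 years in high-risk patients, where an empty arm is least likely. End-stage renal disease is a more plausible low-count outcome, but it is one branch of an either-or endpoint and is not stated as a separate binary test. If it were tested alone at an assumed 10% v 2%, power would be 0.3% by Wald, 2% by Fisher and 6% by mid-P, so changing the test would gain little. All this stands and limits the size of the point.

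Third, one might infer that Wald also loses badly when an arm has one or two events. Against Fisher it does not: at 1 v 7 the P values are 0.045 and 0.049, and at 30% v 10% power is about equal.

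Fourth, sparse-data rules are commonly left to the SAP, which is not shown. That covers an unwritten fallback. It does not cover a method the protocol itself fixes as the sole comparison, and which can fail at the stated sample size.

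**Conclusion.** The point holds in a limited form. The only between-arm method stated for binary outcomes breaks down when an arm of 25 has no events: no finite odds ratio, no log-scale interval for the relative risk, and a P value that runs from 0.0025 to 0.998 at 0 v 6 depending on an unstated choice. The failure is a matter of algebra. How often it would occur rests on assumed risks: 28% for a given arm at 5% risk, 7% at 10%, under 2% at 15% or more. It matters for rare outcomes or a very large effect. When a risk of 30% or 40% is halved, Wald and mid-P power are nearly equal, and there is little to gain. The change is worth making because it is cheap and settles the test before outcomes are seen.

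**What to change.** In Statistical methods, make the treatment comparison for every binary outcome one pre-named unadjusted test that is valid in sparse tables, for example Fisher mid-P, and state the mid-P definition. Report the risk difference and relative risk with Miettinen-Nurminen (score) 95% CIs, which exist with zero cells. Keep logistic regression with risk factors as supportive, fitted with a Firth penalty when any cell is zero or very small.

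Say that the named test decides significance, since it and the score interval can differ in borderline tables: at 0 v 4, mid-P is 0.110/2 = 0.055 while the uncorrected chi-square P is 0.037.

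The cost is some wording and a few lines of code, possibly outside SPSS 19, with no extra patients or data. The main binary comparison would no longer be adjusted for covariates.

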## Introduction

### Background

The number of individuals with type 2 diabetes mellitus (T2DM) in Singapore, a Southeast Asian city-state with a population of 6.5 million, is estimated to grow from 400,000 to 670,000 by 2030 and to an alarming 1.0 million by 2050 with the continuing rise in the prevalence of obesity [1]. Total economic costs per working-age patient with T2DM in 2010 were estimated to be US$5,646, with total economic costs of US$787 million; this is estimated to rise to US$7,791 per patient and total economic costs of US$1,867 million by 2050 [2]. The presence of complications and need for inpatient care are major contributors to these increasing costs. Diabetic nephropathy is a major cause of morbidity and mortality. Asian ethnicity, uncontrolled hypertension and proteinuria are major risk factors for progression to end-stage renal failure [3]. Control of multiple risk factors, as in the Steno-2 study [4], has been shown to improve cardiovascular outcomes, increase the length of time free from incident cardiovascular disease, reduce the risk of death from all causes and reduce the progression of nephropathy as measured by worsening proteinuria, glomerular filtration rate (GFR) and serum creatinine. Previous trials have also suggested the utility of the chronic care model [5], structured recall [6], regular nurse contact [7], technology-enabled diabetes self-management education and support [8, 9] and a multifaceted approach in dealing with diabetes mellitus [6]. While most researchers have agreed that good glycemic outcomes are achievable through committing to appropriate intensive therapy and a team approach [10], there are multiple barriers to the implementation of quality diabetes mellitus care. In particular, barriers to good diabetes mellitus care can include the absence of a system to prioritize clinical resources for patients who require more intensive management, inadequate self-empowerment of patients, inadequate use of effective behavioral modification techniques, ineffective use of technology to enable diabetes self-management education and support and the need to self-fund glucose monitoring devices and monitoring and treatment consumables.

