##### DNE clinic review and telephone reviews

The DNE will counsel the patient at recruitment and follow up the patient’s self-blood glucose monitoring (SBGM) readings and food diary via telephone calls and messages, and in suitable patients who prefer to use a smartphone application, via the “CGH Diabetes Diary” application. Additional face-to-face clinics sessions will be arranged according to clinical discretion. The DNE will prepare a clinic folder for each patient and create a system to facilitate appointment booking and tracking of default. Between each follow-up visit, the DNE will contact the patient by phone or email to remind them of the appointments (e.g. medical follow-up visit or laboratory tests), remind them to adhere to medications and healthy lifestyles, perform and report self- glucose monitoring, advise on insulin dose titration and provide psychosocial support, as appropriate. Before each follow-up visit, the nurse will ensure that results of all blood and urine tests ordered by the physician are available in the clinic review folder for decision making. At each follow-up visit, the patients will first see the nurse to record blood pressure, body weight and urine and blood tests in the clinic review folder. The patient’s compliance will also be checked at each visit. The patients will see the nurse after the folow-up visit, to clarify any issues and concerns. The nurse will reinforce compliance and record any changes in medications, and note any procedures or tests ordered by the doctor. After each follow-up visit, the nurse will issue summary reports to be given to patients and physicians to promote sharing of information.

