##### Equipment, technology and educational material

Equipment will be provided to suitable patients when clinically indicated and these include blood pressure monitors, glucometers, glucose test strips, lancets and android tablets. Patients whose blood pressure readings are not at target at clinic appointments will be taught and encouraged to take measure their own blood pressure and provided with a blood pressure machine. Patients with HbA1c not at target or with significant risks of hypoglycemia will also be provided with a glucometer, glucose tests strips and lancets and taught how and when to perform SBGM, instructed how to use either a written or smartphone logbook, instructed to take photographs of their meals and how to communicate with DNEs via the smartphone application or via messaging systems. Patients will also be taught how to activate smartphone applications or pedometers to measure daily activity. These aim to improve and increase patient-generated health data, communication of capillary blood glucose readings between patient and healthcare professional, diet and exercise, and act as communications channels through which individualized feedback can be given to the patient to specifically target glycemic control, blood pressure and exercise targets. Patients will also be provided with handouts and with tablets containing organized educational material including easy-to-understand and relevant videos and educational material to facilitate diabetes self-care.

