#### Standard care group visits and counseling

Patients randomized to the standard care group will receive usual care, which consists of:
Scheduled, regular, 4-monthly, specialist outpatient care visits for review of blood pressure, HbA1c and other investigations, and titration of medications as per standard of careCounseling with the DNE according to standard of care and usual follow-up via a phone call with the DNE initiated by the patientProvision of educational materials on diabetes mellitus as per standard of careCounseling with the dietitian according to standard of care, based on the American Diabetes Association nutrition therapy recommendations for the management of adults with diabetes mellitus [14]

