#### Secondary endpoints

Secondary outcomes include (1) proportion of patients with documented improved control of risk factors and fulfilment of two or more of the “ABC” targets as defined by (a) HbA1c < 7%, (b) blood pressure < 140/90 mmHg and (c) LDL-C < 2.6 mmol/L and/or two of the following changes in risk factor control: (d) at least 0.5% reduction in HbA1c, (e) at least 5 mmHg reduction in systolic BP, (f) at least 0.5 mmol/L reduction in LDL-C, (g) at least 3% reduction in body weight, (2) frequency of hypoglycaemia (in the last 3 months) (3) number of hospitalization days and (4) changes in femoral IMT.

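### Only the intensive arm is described as getting glucose meters and prompted reporting, so the between-arm hypoglycaemia rate may be biased upward in that arm; separately, the Poisson analysis fixes no response to overdispersion

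*Protocol article*

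**What the plan says.** All references are to the protocol article.

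- **Endpoint.** Secondary endpoints lists "frequency of hypoglycaemia (in the last 3 months"), without distinguishing the arms.
- **Analysis.** Statistical methods says "The number of occurrences of hypoglycemia will be analyzed by Poisson regression", and continues: "Measure of deviance will be checked and relative risk (RR) (with 95% CI) will be calculated". The significance threshold is 0.05.
- **Intensive arm.** Under Equipment, technology and educational material: "Patients with HbA1c not at target or with significant risks of hypoglycemia will also be provided with a glucometer, glucose tests strips and lancets". These patients are also taught self-monitoring and given a written or smartphone logbook. Between visits the diabetes nurse educator (DNE) contacts them to "remind them to adhere to medications and healthy lifestyles, perform and report self- glucose monitoring" (DNE clinic review and telephone reviews).
- **Standard care arm.** Patients have 4-monthly specialist visits, DNE and dietitian counselling to the usual standard, educational materials, and "usual follow-up via a phone call with the DNE initiated by" the patient. No study-supplied meter or log is listed. The Background counts "the need to self-fund glucose monitoring devices" among the barriers to good care.
- **Data collection methods.** This section says that the two questionnaires are done in both arms. It names no source for the hypoglycaemia count.
- **Blinding.** Only the analysing statistician is said to be blinded.

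**The concern.** Many low glucose values are mild or without symptoms, and a patient can report those only after measuring. The programme gives one arm the means to measure, a place to record the result and a nurse who asks for it. The outcome is then compared between arms. An identical 3-month question in both arms would not restore balance, because patients with a meter have more to recall. The rate ratio would then mix true risk with detection, in the comparison that readers will use to judge whether intensified glucose lowering carries a hypoglycaemia cost.

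The second issue is separate. Unequal detection shifts the estimate; overdispersion makes its standard error too small. Plain Poisson regression assumes that variance equals mean. The text plans a check of that assumption but does not say what follows if it fails.

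**Working it through.** The plan gives no rate, dispersion, effect size or power for hypoglycaemia, so there is no stated figure to reproduce. The 25 per arm under Sample size concerns eGFR and has no bearing here. Event rates, captured shares and dispersion below are assumptions.

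**1. Who qualifies for a meter.** Entry requires HbA1c of at least 9% (Eligibility criteria), and the HbA1c target is below 7% (Secondary endpoints). Every patient is thus off target at entry, and in effect every intensive-arm patient meets the HbA1c condition for a meter, subject to the same section's proviso about suitability and clinical indication.

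**2. Size of the detection bias.** Let the true rate be the same in both arms, with captured share c_I in the intensive arm and c_C in controls. Then apparent rate ratio = c_I / c_C.

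- c_C = 80%, c_I = 90%: 0.90 / 0.80 = 1.125
- c_C = 70%, c_I = 90%: 0.90 / 0.70 = 1.29
- c_C = 50%, c_I = 90%: 0.90 / 0.50 = 1.80

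**3. How often this would reach p < 0.05.** Assume 25 per arm and 3 true events per patient in the window. For 50% v 90%, expected totals are 25 × 1.5 = 37.5 and 25 × 2.7 = 67.5. Log ratio = ln 1.8 = 0.588; standard error = √(1/37.5 + 1/67.5) = 0.204; ratio of the two = 2.89. The approximate chance of significance is Φ(2.89 − 1.96) = 0.82. Simulation (20,000 trials per setting) gave:

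| Captured share, control v intensive | Poisson counts, Poisson test | Overdispersed counts (gamma shape 1), Poisson test | Same counts, dispersion-scaled test |
|---|---|---|---|
| 80% v 90% | 10% | 32% | 6% |
| 70% v 90% | 27% | 41% | 11% |
| 50% v 90% | 84% | 71% | 36% |

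With 1 true event per patient, the first column becomes 6%, 11% and 38%. Scaling the variance lowers the rejection rate but leaves the expected ratio at 1.125 to 1.80: the model does not correct the bias.

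**4. Overdispersion alone, with no detection difference.** If variance/mean = φ, the nominal 5% Poisson test has approximate size 2 × [1 − Φ(1.96/√φ)].

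- φ = 1: 5%
- φ = 2: 2 × [1 − Φ(1.386)] = 16.6%
- φ = 3: 2 × [1 − Φ(1.132)] = 25.8%

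Simulation at a mean of 2 events with 25 per arm gave 5.0%, 16.0% and 25.0%. The dispersion-scaled test gave 5.0%, 4.7% and 4.9%.

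**5. What the deviance check would show.** At a mean of 2, a formal 5% deviance test flags 97% of trials at φ = 2 and over 99% at φ = 3. It also flags 16% of trials whose counts are truly Poisson. The check would usually detect dispersion of this size, so the inflation in step 4 arises mainly if its result is not acted on.

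**The case against.** The strongest reply is that the article never says how hypoglycaemia is counted. A reader might infer that events come from meters and logs in one arm and by usual means in the other. The documents do not support that: meters and logs are described as tools of the intervention, there is one endpoint with one look-back, and this fits a question put to everyone. The assessment schedule is a figure that is not shown here, and an article may leave collection forms to the full protocol. This reply stands against any claim of different counting methods. It does not remove the point, because a common question still draws on unequal knowledge of mild or silent events.

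The contrast between arms can also be overdrawn. Controls receive usual nurse counselling and can telephone, nothing says that they lack meters, and the remark on self-funding implies that some may own one. Equipment goes to suitable patients. The gap may therefore be small, as in the 80% v 90% case.

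A reader might also infer a further bias from a 3-month look-back at 4-monthly control visits, which leaves one month in four unseen. That needs continuous counting in the other arm, which is nowhere stated. With the same window in both arms the gap cancels, and an unobserved month does not bias a rate per observed time.

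On the model, a deviance check is planned, the response to it could sit in an analysis plan not shown, and the article gives no evidence that these counts are overdispersed. An unconditional statement that the test rejects too often is therefore not supported.

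Finally, this is one of four secondary outcomes in a 50-patient pilot. Events leading to admission are already captured as serious adverse events and, in part, as hospitalization days.

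**Conclusion.** The point holds in limited form. By design, the arms as described differ in the means of detecting and reporting low glucose, and no arm-neutral ascertainment is described for an outcome compared between them. With equal true rates, the recorded rate may be biased upward in the intensive arm by the ratio of captured shares: 1.125 to 1.80 for the assumed pairs. That the programme will look more harmful does not follow. The shares are unknown, and a true difference in either direction would combine with the bias.

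The model point is conditional. Type I error is about 16% to 25% if variance/mean is 2 to 3 and the deviance check is not acted on; it is close to 5% if counts are Poisson or the variance is scaled. The detection issue matters more, because no choice of count model can repair it.

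**What to change.** 1. Base the between-arm comparison on events whose detection does not depend on a meter, such as hypoglycaemia needing another person's help, emergency attendance or admission. Put the same 3-month question at the same scheduled visits in both arms, and state which look-back windows enter the count.
2. Report meter-detected events by arm descriptively, without a between-arm test.
3. Use negative binomial or dispersion-scaled Poisson regression from the outset, so that inference does not hang on a preliminary deviance test. Add log observed time as an offset if it differs between patients; with one fixed window for all, the offset is constant and changes nothing.
4. Report the result as a rate ratio, since a count model estimates that and not a relative risk.

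The cost is endpoint and analysis wording plus a common question at visits, with no added patients. The comparative endpoint will contain fewer events and so be less precise. The interval on the log scale widens by about √(variance/mean): hardly at all if counts are Poisson, and by factors of about 1.41 and 1.73 at ratios of 2 and 3, where the plain Poisson interval would be too narrow.
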